#### 2.5.3. Teachers’ sleep behaviour.

To account for potential effects of sleep on cortisol secretion and diurnal patterns, three core aspects of sleep will be assessed: subjective sleep quality, sleep duration, and individual chronotype. Sleep quality will be assessed using the validated *Single-Item Sleep Quality Scale* (SQS), which is a reliable tool for capturing self-reported sleep quality in a single question, using a scale from 0 (terrible) to 10 (excellent) [37]. Sleep duration will be assessed by asking participants to report the total number of hours they slept during the previous night, as well as their approximate time of falling asleep (defined as the time when lights were turned off and no further activities such as using electronic devices were done) and their time of waking up. Individual chronotype will be measured using the *reduced Morningness–Eveningness Questionnaire* (rMEQ), a validated instrument that has been translated into German and enables a reliable classification of the chronotype [38]. It comprises five questions with response options covering different periods in the morning and evening.

#### 2.5.4. Teachers’ emotional well-being.

Teachers’ emotional well-being and affective state are assessed using the German version of the *Positive and Negative Affect Schedule* (PANAS) [39,40]. The PANAS is a widely used, validated self-report instrument that distinguishes between positive and negative affect as two independent dimensions of emotional experience. Its psychometric properties have been confirmed in various populations, including occupational and educational settings [41,42]. The questionnaire consists of 20 items – ten for positive affect and ten for negative affect – rated on a five-point Likert scale from “not at all” to “extremely.” The PANAS has been used in studies investigating teachers’ emotional states in everyday school life, particularly in relation to occupational stress and well-being [43,44], which allows for comparisons.

#### 2.5.5. Teachers’ physical activity and sedentary behaviour.

Teachers’ PA and SB will be objectively assessed using ActiGraph wGT3X-BT accelerometers in accordance with current best practice [45]. The devices are worn on an elastic belt positioned at the right hip at the level of the anterior superior iliac spine and continuously record movement and sedentary time. Participants will wear accelerometers on both EOtC days and classroom teaching days to enable comparisons between settings. The devices provide information on the intensity and duration of PA as well as SB during the day. Activity intensity will be classified according to established cut-points for healthy adults [46,47]. Teachers will wear the accelerometers over a period of four days, including two days with EOtC, in order to obtain a comprehensive activity profile during the school week, as was done in previous EOtC research projects regarding children’s PA [48]. In addition, these measures will be explored in relation to cortisol patterns, given established associations between PA, SB, and HPA axis regulation.

#### 2.5.6 Teachers’ work-related quality of life (WRQoL).

Teachers’ WRQoL will be assessed using the *Copenhagen Psychosocial Questionnaire III* (COPSOQ III). The internationally established instrument has been translated into German and validated for use in occupational health research [49]. The COPSOQ III is widely applied in studies on work-related psychosocial factors and health outcomes, enabling comparability of findings within the educational sector [50,51]. A profession-specific version of the questionnaire will be used, including a general section on workplace characteristics and a teaching-specific section covering work tasks, emotional demands, subjective evaluations of the occupational situation, and health-related aspects of the work environment [51].

#### 2.5.7. Pupils’ socioeconomic status and background.

To assess pupils’ socioeconomic background, parents will be asked to report their socioeconomic status (SES) based on the three dimensions of education, occupation and income. An index is created by adding up the points assigned based on the parents’ statements regarding the dimensions mentioned. Based on the index, a categorization of the children into different status groups will be undertaken. Both the questionnaire and the analysis will be based on the procedure of the KiGGS study [52], creating comparability to a nation-wide study on health of children and adolescents. Additionally, children aged 11 and older will be asked to report their subjective social status (SSS) using the German version of the MacArthur Scale for children [52]. This validated instrument presents a visual ladder to help individuals indicate their perceived position within the social hierarchy, with higher placements reflecting a higher perceived social standing [53]. The measure is recently gaining more attention due to its possible own relevance to the individual health status, especially concerning psychological health outcomes such as psychological well-being [54,55].

In addition, pupils will be asked to report their age and gender, as well as provide information on environmental and lifestyle factors that may indicate greater exposure to nature in everyday life. These include whether they have access to a balcony or garden at home, or whether they own a pet. Pupils will also be asked how long they have participated in EOtC and whether they regularly spend time outdoors after school, as time spent in nature may influence outcomes such as nature connectedness and well-being [56,57].

#### 2.5.8. Pupils’ cognitive performance and stress level during class.

To assess pupils’ cognitive performance, electroencephalography (EEG) is used to provide objective, real-time insights into neural processes associated with attention, cognitive load, and engagement.

For this purpose, a mobile EEG system (EPOC X, EMOTIV) is used, which has been successfully applied in previous research investigating cognitive processes in school contexts [58–60]. Growing evidence supports the use of the EMOTIV EPOC in capturing neural responses to cognitive demands in children. It has been employed to detect intervention effects on brain activity during attention tasks [58], to assess learning and emotional states via spectral power analysis [59], and to map brain connectivity during tasks requiring attention and creativity [60]. These findings support the validity of using the EPOC X system for EEG measurements related to attention and cognitive load in children. The EEG device features 14 channels for capturing neural activity, enabling a differentiated analysis of pupils’ cognitive states. To control for individual variability, data are collected intra-individually, with each pupil serving as their own control. EEG recordings are conducted under comparable contextual conditions, namely the same subject, the same teacher, and the same time frame, both during EOtC sessions and classroom teaching.

To control for potential stress induced by wearing the EEG device itself, children’s perceived stress is assessed using a visual analogue scale (0 = “not stressed at all” to 10 = “extremely stressed”). Similar approaches have been applied in studies investigating the stress-reducing effects of multisensory environmental stimuli [61,62].

#### 2.5.9. Pupils‘school-related well-being.

School-related well-being will be assessed using the German version of the *EPOCH-G-S* questionnaire [63], a self-report instrument developed to capture multidimensional aspects of adolescent well-being in the school context. It consists of 19 items across five subscales – Engagement, Perseverance, Optimism, Connectedness, and Happiness – each rated on a five-point Likert scale from “not true at all” to “completely true.” The EPOCH-G-S has shown initial validity in educational research, particularly in studies exploring associations with academic performance, achievement motivation, and self-esteem [64,65]. Its multidimensional and context-specific structure allows for a differentiated assessment of well-being that addresses school-related experiences and psychosocial outcomes. Since the validated age range for the scale is 10–18 years and the target sample in this study comprises children aged 8 years, a cognitive pretest with structured interviews is conducted to assess the comprehensibility of the items and to ensure content validity for younger age groups.

#### 2.5.10. Pupils’ fulfillment of Basic Psychological Needs and views on nature relatedness as a new Basic Psychological Need.

The satisfaction of pupils’ BPN within the educational setting will be assessed using the *Basic Psychological Needs in the Classroom Scale* (BPN-CS; [66]. The 17-item scale includes four subscales – autonomy, competence, relatedness, and novelty satisfaction – rated on a five-point Likert scale from “strongly disagree” to “strongly agree.” It has been validated for use in children aged 8–13 years. The questionnaire offers a structured, age-appropriate measure of need satisfaction within the classroom context and has been used in comparable studies [67–69].

To examine whether the concept of nature relatedness may represent an additional individually perceived psychological need in the context of Basic Psychological Needs Theory [70–72], focus group interviews will be conducted. These interviews will follow a semi-structured guide and aim to generate insights that will inform potential development and inclusion of a new subscale in the translated version of the BPN-CS.

### 2.6. Measures Ecology

#### 2.6.1. Structure and features of outside learning environments.

At each chosen EOtC site, biodiversity is recorded in the form of avian species richness, tree and shrub species richness and characteristic spring ephemerals species richness. To describe structural complexity, forest development stages according to Hilmers et al. (2018) are documented where applicable (in forests) and the amount of deadwood is quantified [73]. Each site is additionally evaluated using a standardized ecological value score, adapted from the Bavarian Compensation Ordinance (BayKompV) [74]. Where applicable, canopy cover is estimated based on upward-facing photographs, from which the percentage of tree crown coverage is calculated using image analysis. Furthermore, the type and number of human-made habitats resulting from EOtC activities (e.g., insect hotels, bird nest boxes, hedgehog piles and more) are recorded at each site. This multi-faceted ecological assessment provides the basis for categorizing the learning sites according to their structural and species richness, serving as a foundation for subsequent analysis of their potential influence on pupils ‘and teachers‘ nature connectedness, species knowledge, well-being and experienced moments of resonance.

#### 2.6.2. Pupils’ and teachers’ nature connectedness.

Both pupils’ and teachers’ nature connectedness will be measured using the *Illustrated Inclusion of Nature in Self Scale* (IINS) [75]. The IINS is a single-item, pictorial measure validated and is used for children aged 9–14, including those with learning difficulties [76,77]. Due to its single item structure and illustrated form, it is easy to understand and is suited for use in different cultures and age groups as well as for people with a lower level of imagination or abstraction. However, because of its simplicity, it cannot be tested for its internal consistency [75,78]. Therefore, the *Nature Connection Index* (NCI) is also included in the questionnaire. The NCI is a standardized tool, which is available in German language. It includes six items and shows long-term changes with stable results in both children and adults [79,80]. In this questionnaire, participants assess six statements using a seven-part Likert scale to specify their level of agreement or disagreement. For making sure that children understand the levels of agreement, coloured smileys are added to the scale.

#### 2.6.3. Pupils’ and teachers’ appreciation of nature.

The shortened, German version of the *2-MEV* (2-major environmental values model) questionnaire, which was validated by Randler and colleagues in 2024, was included in our survey [81]. Similar to the NCI, agreement levels are stated about six different statements by participants on a five level Likert scale, including smileys for younger participants.

#### 2.6.4. Pupils’ and teachers’ species knowledge.

Since it has been shown that knowledge of local species increases children’s appreciation of these species [82] a combination of native species found throughout Germany was selected for this study, excluding mammals. Identification rates of mammals have been shown to be highest when species knowledge was tested in the past, being the most phylogenetic similar to humans and present in children’s books and television [83]. Therefore, the query focuses on other species, covering trees, shrubs, flowering plants, insects, one of each a nematode and a spider as well as two bird species, showing coloured pictures of the respective species in an open-ended item format. For each species, one photograph as well as one or two sketches are shown to ensure a detailed depicture of the species. Participants can gain 1 point for each species named, up to a maximum of 25 points, and 0.5 points if they cannot give the exact name of the species but can only indicate a higher taxonomic group.

### 2.7. Measures Social Interactions and Special Needs

#### 2.7.1. Reconstructive teaching and learning analysis.

In contrast to research based on subsumptive logic, reconstructive classroom research seeks the structure of meaning inherent in protocols of events. It is based on written records of teaching practice and aims at uncovering latent structures of meaning [84] through interactional analysis [85], documentational analysis [86], in-depth hermeneutic analysis [87], and objective hermeneutic analysis [88,89]. For this reason, weekly EOtC lessons at individual schools are recorded using three cameras installed at the learning location. In addition, at least two lessons per week are videotaped in the classroom, whereby care is taken to ensure that the lessons are taught by the same teacher. This allows differences in teaching and learning processes between EOtC and classroom teaching to be systematically reconstructed. Special attention is given to pupils with special educational needs, as most of the participating classes for video recording are from special-needs schools, making it possible to examine how EOtC lessons may foster inclusion and tailored learning processes in this context. The analysis is guided by the question of whether the change of location results in different practices and how these differences and their practical consequences can be described in terms of teaching and learning. The didactic triangle [90] serves as a guide when examining the relationships between teacher and pupil, between pupil and subject matter, and between teacher and subject matter.

BPN-CS	Fulfillment of BPN	Pupils	Once p. school year	Quantitative	Health
EPOCH-G-S	School-related well-being	Pupils	Once p. school year	Quantitative	Health
Cognitive Interviews	Validation of EPOCH-G-S for younger pupils	Pupils	Once p. school year	Qualitative	Health
COPSOQ III	WRQoL	Teachers	Once p. school year	Quantitative	Health
EEG	Cognitive performance	Pupils	Once p. school year: 1 EOtC day and 1 regular day	Quantitative	Health
PANAS	Emotional well-being	Teachers	2^nd^ half of the school year: 5x p. day, 2 EOtC days and 2 regular days	Quantitative	Health
rMEQ	Sleep chronotype	Teachers	Once p. school year	Quantitative	Health
Salivary cortisol	Physiological stress	Teachers	2^nd^ half of the school year: 5x p. day, 2 EOtC days and 2 regular days	Quantitative	Health
Stress scale	Subjective stress level	Pupils	Once during EEG measurement	Quantitative	Health
SQS	Sleep quality	Teachers	Each morning with cortisol samples	Quantitative	Health
OPTIS	Instructional quality/ applied teaching principles	Teachers and pupils	Once p. school year: 1 EOtC day and 1 regular day	Quantitative	Pedagogy
Video and audio recordings	Teaching and learning analysis	Teachers and pupils	Once p. school week: 1 EOtC day and 1 regular day	Qualitative	Sociology & School Pedagogy

### 2.8. Data analysis

#### 2.8.1. Statistical analysis.

To evaluate the quantitative data of WRQoL, emotional well-being, psychological well-being, nature connectedness, appreciation of nature, PA and SB descriptive analyses will be carried out, in order to present central tendencies and distributions of the variables collected. Inferential statistical methods and repeated measures analysis of variance will be used to test group differences and hypotheses. To make sure the data structure enables this procedure, the data will be checked for normal distribution and homogeneity of variance before the analysis.

To investigate the relationship between the ecological features of the learning environments and other study variables correlation analyses, linear regression models and possibly generalized linear models or mixed-effect models will be used in order to take possible hierarchical structures of the data into account.

Linear mixed models will be used for the cortisol measurements to adequately account for intra-individual changes and covariates such as sleep quality or chronotype. In addition to descriptive analyses of the collected data, Bayesian Hierarchical Linear Models will be used to investigate the influence of PA and SB on cortisol levels.

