**Methods:**

This study protocol describes an exploratory, quasi-experimental, interdisciplinary study conducted in a total of 33 schools throughout Germany. Data collection will be carried out from September 2025 to November 2026. The first results of the data collection are expected in October 2026. It includes approximately 50 EOtC teachers, 50 non-EOtC teachers, 50 EOtC classes, and 18 non-EOtC classes with for intra- and interindividual comparisons. Data collection covers aspects from the fields of health, ecology, school pedagogy, and sociology and includes both pupils and teachers as target groups, as well as the various outdoor learning environments. For pupils and teachers, the study examines the effects of EOtC on nature connectedness, appreciation of nature, and plant and animal species knowledge. This is assessed twice per school year with questionnaires and compared to control classes within the same schools. In addition, for pupils, cognitive performance, measured by electroencephalography (EEG), school-related well-being, and basic psychological needs – both assessed via questionnaires – will be analysed. For teachers, stress levels, emotional well-being, and physical activity will be assessed using salivary cortisol samples, accelerometery, and questionnaires on both EOtC and regular teaching days, enabling intraindividual analyses. Moreover, teaching characteristics will be documented, and video-based analyses of social interactions between teachers, pupils, the outdoor learning environment, and teaching objects are conducted. Finally, biodiversity at the outdoor learning sites and their effects on the other study variables (e.g., nature connectedness, appreciation of nature, species knowledge and well-being of pupils and teachers) will be statistically analysed.

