
**Fig 1 pone.0337524.g001:**
[figure not shown]
Stages of recruitment.

This results in expectedly 36 schools with approximately 50 EOtC teachers, 50 non-EOtC teachers, 50 EOtC classes, and 18 non-EOtC classes (Fig 2). All participants provide written informed consent prior to taking part in the study. Each participant receives detailed written information about the study’s aims, procedures, and data protection measures. In the case of child participants, written consent is obtained both from the children themselves (age-appropriate assent) and from their parents or legal guardians. All data are pseudonymized using individual participant codes, which are self-generated by the participants to ensure confidentiality. The research team has no direct access to personal identifiers.

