## 3. Discussion

The aim of this methods paper was to present a large-scale, interdisciplinary research project on EOtC in Germany. By describing the disciplines involved, as well as the survey methods, the analysis strategies, and the planned timeline, the paper aims to provide a comprehensive overview of the study concept. The interdisciplinary nature of the project enables us to examine the multifaceted effects of EOtC on health, social interaction, pedagogical processes, and ecological aspects of all participants within a comprehensive context. While the exploratory, interdisciplinary approach offers several advantages, the study specifically follows a parallel multi-strand research approach, combining independent quantitative and qualitative sub-studies conducted within the same overarching project. The quantitative component is based on a multi-level, predominantly cross-sectional design and was chosen to reflect authentic school conditions with minimal disruption to everyday teaching practice, thereby ensuring high ecological validity. At the same time, it enables comparability through the use of control groups where feasible and intra-individual approaches where experimental control is limited. The qualitative component follows a Grounded Theory approach based on video data, aiming to reconstruct processes of teaching and learning in outdoor contexts. Both strands address distinct research questions and are primarily analysed independently. This approach offers several advantages but also comes with certain limitations, which are discussed later in the discussion.

The chosen design represents a central strength of the project. It enables the inclusion of all disciplines involved and the survey measures, such as the observation of teaching characteristics (OPTIS) and the video-based analysis of social interactions between teachers, pupils, the EOtC-learning environment, and teaching objects. To our knowledge, this is the first EOtC study to document and examine EOtC teaching in such detail. In addition, the selected ecological investigations have not yet been carried out in this depth, with the intensive examination of the EOtC-learning environments representing a particular novelty in the field. This allows observed effects to be linked retrospectively to specific teaching processes.

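### Pupil EOtC-versus-control comparisons are planned without a class or school term, and mixed models for site features are left optional, so standard errors for these effects would be too small if the plan is followed as written

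*Protocol article*

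**What the plan says.** The first paragraph of section 2.8.1 covers work-related quality of life (WRQoL), emotional and psychological well-being, nature connectedness, appreciation of nature, physical activity (PA) and sedentary behaviour (SB). For these, "Inferential statistical methods and repeated measures analysis of variance will be used to test group differences and hypotheses". The suitability of the data is to be judged on two checks: "the data will be checked for normal distribution and homogeneity of variance before the analysis".

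For the ecological features of the learning sites, "correlation analyses, linear regression models and possibly generalized linear models or mixed-effect models will be used", with the stated purpose "in order to take possible hierarchical structures of the data into account".

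Cortisol is treated differently: "Linear mixed models will be used for the cortisol measurements to adequately account for intra-individual changes and covariates such as sleep quality or chronotype".

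On the structure of the data, the Abstract (Methods) says that nature connectedness, appreciation of nature and species knowledge are surveyed twice per school year and "compared to control classes within the same schools". Section 2.3 expects "36 schools with approximately 50 EOtC teachers, 50 non-EOtC teachers, 50 EOtC classes, and 18 non-EOtC classes"; the Abstract gives 33 schools. Section 2.2.2 has the biodiversity of the learning areas surveyed a single time in the year, at selected schools. The Discussion states: "The quantitative component is based on a multi-level, predominantly cross-sectional design".

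**The concern.** A pupil is exposed to EOtC because the class is, and classmates share teacher, site and lessons. Their answers are therefore likely to be correlated. Repeated-measures ANOVA allows for the correlation between one pupil's two measurements, but not for the correlation between classmates. Neither of the two named checks bears on independence, which is the assumption that this design breaks. The same holds more strongly for biodiversity or structural complexity, where everyone taught at a site carries one value of the predictor.

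If pupils are counted as independent, chance differences between a limited number of classes (only 18 of them controls) or sites can be reported as effects of EOtC or biodiversity. The ecological research questions in the Introduction ask whether EOtC and site biodiversity lead to higher knowledge, connectedness and appreciation, so the precision of these estimates matters.

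**Working it through.** **Which outcomes are affected.** The listed outcomes differ in where the exposure varies (research questions in the Introduction, sections 2.1.1 and 2.5.5, Table 1):

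- Pupils' nature connectedness and appreciation of nature: EOtC versus control classes, two waves. The exposure is at class level, so these are affected.
- Site features as predictors: the exposure is at site level, so these are affected.
- PANAS, PA and SB: two EOtC days and two regular days in the same teacher. The exposure varies by day, and repeated-measures ANOVA suits it.
- WRQoL: between teachers, measured once. With 100 teachers in 36 or 33 schools there are 2.8 to 3.0 per school, so clustering matters little.

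**Inputs.** From the article: 50 EOtC and 18 control classes (68 in all), and 36 (or 33) schools. The article states no power calculation, alpha, ICC or class size, so there is no figure of its own to reproduce. Assumed: two-sided 5% test, m = 10 to 25 participating pupils per class, ICC 0.01 to 0.20.

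**Formulas.** Design effect DE = 1 + (m − 1) × ICC. The true standard error is √DE times the reported one. Actual type I error = 2 × [1 − Φ(1.96/√DE)].

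**Class-level difference at one time point, pupils treated as independent.** Each cell gives DE and actual type I error.

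| m | ICC 0.01 | ICC 0.05 | ICC 0.10 | ICC 0.20 |
|---|---|---|---|---|
| 10 | 1.09; 6.0% | 1.45; 10.4% | 1.90; 15.5% | 2.80; 24.1% |
| 20 | 1.19; 7.2% | 1.95; 16.0% | 2.90; 25.0% | 4.80; 37.1% |
| 25 | 1.24; 7.8% | 2.20; 18.6% | 3.40; 28.8% | 5.80; 41.6% |

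Example: m = 20 and ICC 0.05 give DE = 1 + 19 × 0.05 = 1.95 and √1.95 = 1.40. The 68 × 20 = 1,360 pupils then carry the information of 1,360/1.95 ≈ 697.

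**Site-level predictor.** If the 50 EOtC classes were spread over 36 sites with m = 20, there would be 50 × 20/36 ≈ 28 pupils per site. ICC 0.05 to 0.10 then gives DE 2.34 to 3.68 and an actual error of 20% to 31%; with 33 schools it is 21% to 32%. This is only illustrative, because the article maps selected schools and does not give the number of sites.

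**Simulation check** (2,000 runs per setting; 36 schools, 50 and 18 classes, control classes placed in schools that also have EOtC classes). With m = 20 and class and school variance shares of 0.05 each, a pupil-level t-test rejected 17.7% of the time and a pupil-level correlation with a site predictor 29.1%. A t-test on the 68 class means stayed at 2.1% to 5.1% over all settings run. It was conservative when school variance was present, because control classes share schools with EOtC classes. The inflation therefore comes from the choice of analysis and can be removed.

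**Group-by-time test.** Stable class and school differences cancel in the change between waves. The same formula applies, but with the ICC of change in place of the ICC of level. The article does not say which ANOVA term is of interest, so the percentages above do not carry over directly.

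**Teachers, WRQoL.** At 2.8 to 3.0 per school and ICC 0.05 to 0.20, DE is 1.09 to 1.41. Even this overstates the problem where control teachers come from the same schools.

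**The case against.** The strongest reply is that the article is condensed and its wording open. Its reference to inferential methods in general does not exclude cluster-aware models, and the detail of random effects is commonly left to an analysis plan that is not shown. The Discussion calls the design multi-level and concedes that class and school differences cannot be fully controlled. The study is declared exploratory, with no stated alpha or power claim to invalidate. This tempers the consequence. It does not remove the point, because the paragraph does name a method and does name the checks that are meant to justify it, and neither reaches classes or schools. Exploratory intervals also need valid standard errors.

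A reader might infer more than the documents support:

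- *That the plan ignores clustering throughout.* It does not. For site features it names mixed models for exactly this purpose and leaves them optional, and cortisol has a firm mixed model. The fault in the site analyses is lack of commitment.
- *That the teacher results are invalid.* PANAS, PA and SB are paired within teachers, and WRQoL has about three teachers per school.
- *That all p-values will be far too optimistic.* Without an ICC or class size this is not established. At ICC 0.01 and 10 pupils per class the error is about 6%, and the calculation concerns a single time point.

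**Conclusion.** The point holds for two sets of analyses: pupil outcomes compared between EOtC and control classes, chiefly nature connectedness and appreciation of nature, and analyses with a site feature as predictor. Analysed as written, their standard errors are too small. For a class-level difference at one time point, the understatement is a factor of 1.04 to 2.41 (√1.09 to √5.80) and the actual error of a nominal 5% test is about 6% to 42%; the middle of the assumed range, ICC 0.05 to 0.10 with 20 pupils per class, gives 16% to 25%. All of these rest on assumed ICCs and class sizes. For a group-by-time test the inflation could be smaller and depends on the clustering of change. The number of top-level clusters is itself uncertain while 33 and 36 schools both stand in the article.

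**What to change.** - **Pupil EOtC-versus-control comparisons.** Commit to linear mixed models with random intercepts for school and class and small-sample degrees of freedom. Where outcomes are measured twice, add a pupil intercept and a class-by-wave term, with EOtC, wave and their interaction as fixed effects, and state which effect answers the question. For outcomes measured once, omit the wave and pupil terms. A class-level or cluster-robust analysis is an acceptable alternative.
- **Site-feature predictors.** Delete the word that makes mixed models optional, require a site or school random intercept, and report simple correlations only on site means.
- **Teachers.** Keep the paired within-teacher analysis for PANAS, PA and SB. A school term for WRQoL is optional.
- **School count.** Reconcile 33 and 36.

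The cost is a revision of two paragraphs, slightly more analysis work and wider intervals. No new data are needed, and section 2.4 expects first results only in October 2026, so the change can be made before they are reported.
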